**5.- Methodology**

**5.1.- Study design**

A randomized, patient- and data analyst-blinded clinical trial to compare outcomes in terms of the lactate clearance rates (quantity/unit of time) of the assigned therapy groups. Two treatment groups will be established: one control group without hemofiltration (CG or 1), one group with hemofiltration using a polysulfone filter (PG or 2).

To ensure an unbiased assessment of treatments, randomization will be performed in eight blocks of five patients. The study groups will be equivalent in all aspects except the procedures they undergo.

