**2.- Purpose**

The purpose of the research is to determine whether, by controlling the patient's hemodilution level and, therefore, the acute anemia caused by the CPB priming fluid, continuous conventional ultrafiltration (CUF) can decrease serum lactate levels during normothermic CPB by increasing the hematocrit and, consequently, the supply of oxygen to the tissues, and whether the hemofiltration membrane can remove lactate molecules in situations of HL in CPB.

This will be done by performing arterial and venous blood gas analyses every 20 minutes during CPB to measure blood lactate levels, pH, oxygen delivery (DO2), oxygen consumption (VO2), oxygen extraction (ERO2), venous oxygen saturation (SvO2), arterial and venous carbon dioxide difference (△pCO2) and lactate levels in the effluent from the hemoconcentrator.

The perfusionist's role is essential during the procedure, as they control both Cardiac Output (CO) and gas exchange, as well as a number of variables that, depending on their action, will affect blood lactate levels.

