MUF seeks to achieve more effective hemofiltration by hemoconcentrating the patient and reducing inflammatory mediators [12].

The surgical team at Puerta del Mar University Hospital who are taking part in the research usually use a polysulfone membrane throughout the procedure and perform high-flow continuous ultrafiltration (UF), replacing the filtered volume with Prismasol 2® pharmaceutical solution, which contains the following active substances: calcium chloride, dihydrate; magnesium chloride, hexahydrate; glucose monohydrate, lactic acid solution 90%; sodium chloride; potassium chloride and sodium hydrogen carbonate. This solution is also used for priming the CPB circuit, and it must be taken into account in the research that Prismasol 2® solution contains 3 mEq/L of lactate.

Prismasol 2® solution is used as a solution for hemofiltration in the treatment of renal insufficiency and no contraindications with CPB have been reported, since serum potassium and calcium levels are monitored every 20 minutes. The administration of sodium bicarbonate is also eliminated from priming.

Likewise, CUF during CPB is safe thanks to continuous patient monitoring throughout the procedure.

The flow rates recommended by the manufacturer for the replacement solution in hemofiltration and hemodiafiltration are as follows: Adults and adolescents: 500 - 3000 ml/hour.

The use of hemofiltration in adults during CPB procedures has evolved over the years, with studies showing the advantages of CUF or MUF in CPB procedures, such as increased hematocrit with the consequent reduction in blood transfusions, reduction of inflammatory response, improvement of hemodynamic parameters and better neurological outcomes in patients, as well as a shorter postoperative intubation time in the intensive care unit [13].

There is a disparity in the scientific literature regarding HL during and after CPB, and while Soliman R et al. [14] consider that continuous hemofiltration increases postoperative lactate levels and inotropic drug use, Kiziltepe et al. [15] describe it as a safe procedure in adult patients undergoing cardiac surgery.

Perhaps the results of the Soliman group were conditioned by the use of moderately hypothermic CPB and the use of Ringer's lactate solution at a concentration of 27.8 mEq/L for priming the CPB circuit.

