**4.2.- Hypothesis:**

- Continuous ultrafiltration with volume replacement using a polysulfone membrane during CPB in patients undergoing cardiac surgery decreases intraoperative lactatemia.
- Patients undergoing cardiac surgery and continuous ultrafiltration with volume replacement using a polysulfone membrane have a lower postoperative morbidity and mortality rate than patients undergoing cardiac surgery without hemofiltration.
- Patients undergoing cardiac surgery and continuous ultrafiltration with volume replacement using a polysulfone membrane have a better health status after surgery than patients undergoing cardiac surgery without hemofiltration. (Assessed by NNN taxonomies: NANDA, NOC, NIC).

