**4.3.- General objectives:**

- To determine whether continuous ultrafiltration with volume replacement using a polysulfone membrane during CPB in patients undergoing cardiac surgery decreases intraoperative lactatemia.
- To assess morbidity and mortality with the use of CPB and continuous hemofiltration.
- To evaluate the health status of patients before and after surgery with CPB using the NNN taxonomies (NANDA, NOC, NIC).

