**5.4.- Description of methods:**

The proposed methods to be used in this study are based on analyses of the following instruments and variables:

- Clinical and analytical instruments.
- Record sheet of variables from the patient's medical record.
- Record sheet of intraoperative variables.
- Graph from the perfusionist and electronic data collection systems.
- Record sheet of postoperative variables.
  - Graph and records from the ICU.
  - Graph and records from the ward.
  - Lactate testing instruments.

The variables to be studied have been selected according to the existing literature regarding the factors associated with the results of the therapy used.

- Dependent variables:
  - Levels of serum lactate in mmol/L (continuous quantitative variable): at the beginning of CPB, after 10 minutes of CPB, every 20 minutes during the procedure and 20 minutes after the end of CPB.
  - Effluent lactate levels in mmol/L (continuous quantitative variable): at the end of the procedure.
  - Intra- or perioperative mortality, yes/no (dichotomous variable).
  - Complications: intubation, seizures, pleural effusion requiring drainage, yes/no (dichotomous variable).
  - Evaluation of the outcome of the intervention by the perfusionist nurse. During CPB. NOC nursing taxonomy in the preoperative period, at the end of each procedure and in the postoperative period. These outcomes consist of indicators that measure the patient's health on a Likert scale (1-5).
- Adjustment or stratification variables:
  - Predicted mortality scale (EuroSCORE[[1]](#footnote-2)).
  - Serum potassium and lactate values, immediately after surgery and with each routine blood analysis in the ICU.
- Preoperative variables:
  - Demographic variables:
    - Age: years (quantitative variable).
    - Sex: male/female (dichotomous variable).
- Biometric variables:
  - Height: centimeters (continuous variable).
  - Weight: kilograms (continuous variable).
    - The above variables will be used to calculate the body mass index (BMI): weight/height2 = kilograms/m2 (continuous variable).
- Biochemical variables:
  - Glucose: mg/dL (continuous variable).
  - Serum lactate: mmol/L (continuous variable).
  - Diagnosis upon admission: according to ICD-9 international classification.
    - Comorbidities: presence/absence in the patient's medical record (dichotomous variables):
      - Arterial hypertension.
      - Hyperlipidemia.
      - Peripheral artery disease.

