**5.8.- Limitations of the study and ethical considerations**

The study design does not allow the use of total blinding, and the perfusionist is aware of the therapy and characteristics of the membrane at all times. According to the literature and standard practice in this country, the use of a control group should not pose any ethical dilemma if certain premises are taken into account.

The only condition that the control group must meet is that the patients must be able to manage their fluid balance by themselves, as a fluid overload has been shown to be harmful. This may mean that the patients in the control group have better renal function than those in the other group, or at least better initial diuresis. However, the primary objective is not to measure or evaluate perioperative renal function. In addition, a hemofilter will be available for use if control patients are not able to manage their fluid balance through diuresis. Finally, if surgery times are shorter in the control group, the lactatemia levels may be lower than in the other group with a longer duration. If this is the case, we will stratify the treatment groups by selecting cases with a shorter duration. In any case, a minimum time of 60 minutes is established from start of CPB + CUF and to the end of CPB.

It will be carried out according to the international ethical recommendations (the Declaration of Helsinki and the Oviedo Convention), since the use of the best available therapy according to the patients' circumstances is contemplated at all times.

In order to safeguard confidentiality, all personal data collected as part of this study will be treated in accordance with Organic Law 15/1999, of December 13, on personal data protection.

Likewise, informed consent will be requested for surgery that includes the usual CPB procedures with or without hemofiltration.

Informed consent will also be requested for use of any data deriving from medical records and analytical determinations. Access to personal information will be restricted to the investigator and authorized personnel and all of them will be obliged to maintain confidentiality. If the work is published, the patients' identity will remain anonymous at all times.

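### Section 5.1 compares the arms on an undefined lactate clearance rate that is neither the hypothesis variable nor a listed outcome, and no outcome or analysis uses the infused lactate that Section 3 flags

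*Protocol*

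**What the plan says.** The design statement (Protocol 5.1) describes a trial "to compare outcomes in terms of the lactate clearance rates (quantity/unit of time) of the assigned therapy groups". It gives no formula. One arm has no hemofiltration; the other has a polysulfone filter. For controls, Section 5.8 adds only that "a hemofilter will be available for use if control patients are not able to manage their fluid balance through diuresis".

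The first hypothesis (4.2) is that ultrafiltration with volume replacement "during CPB in patients undergoing cardiac surgery decreases intraoperative lactatemia". The first general objective (4.3) asks the same thing. The lactate variables among the dependent variables in 5.4 are both concentrations: serum lactate in mmol/L, taken serially from the start of cardiopulmonary bypass (CPB), and "Effluent lactate levels in mmol/L (continuous quantitative variable): at the end of the procedure". Neither 5.4 nor the analysis section (5.7) mentions a clearance rate.

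On the replacement fluid, Section 3 states that "it must be taken into account in the research that Prismasol 2® solution contains 3 mEq/L of lactate". It also gives zero net fluid balance as the goal. Section 5.4 records the effluent volume (VTot), the replacement volume (VolR) and the hemofiltration time. No outcome definition or analysis step combines these with the lactate content of the fluid.

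**The concern.** The sentence that says what the arms are compared on names a different quantity from the hypothesis, the objective and the variable list. Whoever writes the analysis cannot tell which governs, and the choice could be made after the data are seen.

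Neither available meaning of clearance repairs this. A quantity per unit time, taken literally, is a mass-removal rate, and controls without a filter have no effluent. The fall in serum lactate per unit time can be computed in both arms, but it mixes the effect with starting value and elapsed time. Section 5.8 itself expects that surgery times may differ between arms and shift lactate levels.

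The second issue concerns how filter removal would be read. Effluent lactate reported alone is gross removal. The same circuit returns lactate in the replacement fluid, so a positive gross figure can coexist with a net load from the circuit.

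**Working it through.** The protocol gives no clearance or net-lactate figure to reproduce. The check has two parts.

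**1. Which variable is compared**

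| Place | Quantity | Available in controls? |
|---|---|---|
| 5.1 | clearance rate, quantity per time, no formula | not as mass removal; yes as serum decline |
| 4.2, 4.3 | intraoperative blood lactate level | yes |
| 5.4 | serum lactate, mmol/L, serial | yes |
| 5.4 | effluent lactate, mmol/L, at the end | no (no filter) |
| 5.7 | change from first sample; tests between groups | clearance not named |

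The serum-decline reading can rank patients against the hypothesis (illustrative values). A patient falling from 4 to 3 mmol/L in 1 h scores (4 − 3)/1 = 1.0 mmol/L per h. The same fall over 2 h scores 0.5. A patient steady at 1.5 mmol/L scores 0, the worst rate with the lowest level.

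**2. Lactate balance across the filter circuit**

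Inputs from the protocol:
- Replacement lactate is 3 mEq/L, which equals 3 mmol/L for a monovalent ion (Section 3).
- Replacement flow is 500 to 3000 ml/h (Section 3). High-flow ultrafiltration is at least 35 ml/kg/h, with partial or full replacement (Annex IV).
- Zero net balance is the goal (Section 3).
- Normal serum lactate is below 2 mmol/L; levels above 4 mmol/L are linked to morbidity and mortality (Section 3).

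Assumptions not in the protocol: sieving coefficient S = 1 (range 0.9 to 1.0), body weight 80 kg, and replacement ratio r = VolR/VTot = 1 (range 0.5 to 1).

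Formulas, with C the serum lactate:
- gross removal = VTot × S × C
- infused = VolR × 3
- net removal = VTot × S × C − VolR × 3
- break-even C = 3r/S

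With r = 1 and S = 1, net removal = Q × (C − 3), where Q is the flow. At 35 ml/kg/h and 80 kg, Q = 2.8 L/h. Results in mmol/h:

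| Q (L/h) | Infused | C = 1.5: gross / net | C = 2: gross / net | C = 3: gross / net | C = 4: gross / net |
|---|---|---|---|---|---|
| 0.5 | 1.5 | 0.75 / −0.75 | 1.0 / −0.5 | 1.5 / 0 | 2.0 / +0.5 |
| 2.8 | 8.4 | 4.2 / −4.2 | 5.6 / −2.8 | 8.4 / 0 | 11.2 / +2.8 |
| 3.0 | 9.0 | 4.5 / −4.5 | 6.0 / −3.0 | 9.0 / 0 | 12.0 / +3.0 |

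The sign does not depend on flow. At C = 4 the gross figure is 4/(4 − 3) = 4 times the net figure.

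Break-even serum lactate (mmol/L):

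| r | S = 1.0 | S = 0.9 |
|---|---|---|
| 1.0 | 3.0 | 3.33 |
| 0.8 | 2.4 | 2.67 |
| 0.5 | 1.5 | 1.67 |

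**The case against.** The best defence is that the serum-decline meaning is the sensible one. Section 5.1 speaks of both groups, and 5.7 already measures change against the first sample. That quantity exists in controls, and because it is measured in blood it already reflects whatever lactate was infused. This stands: the missing control value and the net-load problem apply only to the mass-removal meaning. What remains is that 5.1 does not say which meaning is intended, that its units point to the other one, and that a rate of decline is still not the level named in 4.2 and 4.3.

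Three stronger readings are tempting, and the protocol does not support them:
- A reader might infer that clearance is the primary outcome. No primary outcome is named, and serum lactate comes first in the hypotheses, objectives and dependent variables.
- A reader might infer that the infused lactate was overlooked. Section 3 flags it explicitly, and 5.4 collects the volumes needed. The gap is that nothing then uses them.
- A reader might infer that the Purpose section poses net balance as its question. It asks whether serum lactate falls, and whether the membrane can remove lactate during hyperlactatemia. Effluent lactate is direct evidence on the second question, and at 4 mmol/L net removal is positive in the scenarios above.

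A formula for a derived variable can also be left to an analysis plan. That is fair for the formula, but not for a design statement that conflicts with the hypothesis.

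**Conclusion.** The inconsistency is certain from the text: 5.1 names a comparison that 4.2, 4.3, 5.4 and 5.7 do not carry. Only the mass-removal meaning fails outright in controls.

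The net-load result is conditional. With full replacement and sieving of 1, gross removal is positive during a net load from the circuit for every serum lactate below 3 mmol/L, which includes the whole range the protocol calls normal. Within hyperlactatemia, taken as 2 mmol/L or more, the misleading band is then about 2 to 3 mmol/L. With half replacement and the same sieving, break-even is 1.5 mmol/L and that band disappears. The protocol allows partial replacement, so the size in this trial is unknown until VTot and VolR are seen.

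The share of patients above break-even cannot be estimated: the 10% to 21% hyperlactatemia frequency in Section 3 comes without a lactate cut-off. The calculation concerns the circuit only. It does not show that hemofiltration raises serum lactate, which is what the between-arm serum comparison would test.

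The timing of effluent sampling is a minor matter. Section 2 can be read as placing "lactate levels in the effluent from the hemoconcentrator" in the 20-minute sampling, while 5.4 says the end of the procedure. Section 5.4 is the operative definition.

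**What to change.** 1. In 5.1, replace the clearance rate with serum lactate (mmol/L) in both arms at one fixed elapsed CPB time that every eligible patient reaches. Adjust for the serum lactate that 5.4 already schedules at the start of CPB. Section 5.8 gives a 60-minute minimum from the start of CPB with ultrafiltration. Section 5.5 words that minimum differently, so the two should be reconciled before the time is named. Linear regression, already in 5.7, can carry the adjustment, but it should be planned from the outset rather than used only when groups prove unequal.
2. Report filter removal in the hemofiltration arm only, descriptively and net: (VTot × effluent lactate − VolR × 3 mmol/L) / hemofiltration time. State volumes in litres; 5.4 gives thousands and millimeters. The factor of 3 holds for volume given as Prismasol 2, whereas 5.4 describes VolR as a plasma solution, so these descriptions should be made to agree.
3. Measure effluent lactate on the pooled effluent at the end of the procedure, so that one concentration represents the total volume. Align Section 2 with 5.4.

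The cost is wording, one derived variable and a specified effluent sample; the volumes, time and effluent lactate are already planned. No treatment changes. The downside is that reported removal becomes smaller and may be negative.

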**5.6.- Sample size**

The sample size will result from the prospective inclusion of a consecutive series of patients over 10 months who undergo surgery with CPB by the investigator in the Cardiovascular Surgery Unit of Puerta del Mar University Hospital, Cádiz, under normothermic conditions. As a preliminary analysis, this cohort is estimated to consist of about 40 patients in the Cardiovascular Surgery Unit.

The study population will comprise a sample of patients who meet the inclusion criteria between February 2017 and December 2017.

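### Blocks of five cannot be split 1:1 between two arms, and a single fixed block size leaves some allocations knowable in advance to anyone enrolling who knows the block structure

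*Protocol*

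**What the plan says.** Protocol section 5.1 describes "A randomized, patient- and data analyst-blinded clinical trial" with one control group without hemofiltration and one group with a polysulfone filter. It then states, with unbiased assessment as the aim, that "randomization will be performed in eight blocks of five patients". It gives no allocation ratio and no make-up of a block. The same paragraph expects the groups to be equivalent apart from the procedure.

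Section 5.6 gives the size: "this cohort is estimated to consist of about 40 patients in the Cardiovascular Surgery Unit". The patients form a consecutive series at one hospital, described as those "who undergo surgery with CPB by the investigator".

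Section 5.8 concedes that blinding is incomplete, because "the perfusionist is aware of the therapy and characteristics of the membrane at all times". It also attaches a fluid-balance condition to the control group.

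Section 5.5.2 contains two exclusions that can only be confirmed once surgery is under way: a minimum time before decannulation, and a positive fluid balance judged late in bypass.

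**The concern.** Blocking is used to keep the arms level as recruitment proceeds. With two arms and an odd block size it cannot do that within any block. Without a stated ratio or make-up, two people following section 5.1 could build materially different lists.

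The second issue is concealment. Where an operator sees each assignment, a fixed block size that is known to those who enrol lets them work out some later assignments from earlier ones. At a single centre with about 20 patients per arm, a few patients steered in or out could affect the comparison. Section 5.8 ties the control arm to patients who can manage their own fluid balance. Staff who anticipated the next allocation would therefore have a patient characteristic to sort on, and one that may bear on lactate.

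**Working it through.** **Inputs.** Two arms, eight blocks of five (5.1); about 40 patients (5.6). The make-up of a block is not stated, so three possibilities are carried: (A) the same 3:2 in every block, (B) 3:2 or 2:3 at random in each block, (C) four blocks of each kind.

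**The plan's own total.** 8 × 5 = 40, which agrees with section 5.6. Nothing in the totals suggests that five is a misprint.

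**Balance.** The closest split of five is 3:2. If k of the eight blocks favour hemofiltration, that arm has 3k + 2(8 − k) = 16 + k patients and the difference between arms is |2k − 8|.

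- A: 24:16.
- B: k is Binomial(8, 0.5). P(20:20) = 70/256 = 27%. P(difference of 4 or more) = 2 × (1 + 8 + 28)/256 = 74/256 = 29%.
- C: exactly 20:20.

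**Cost of the worst split.** The variance ratio is (1/24 + 1/16)/(1/20 + 1/20) = 0.10417/0.10 = 1.042, a 4.2% increase. At an assumed 80% power and two-sided 5% level (the protocol states neither), the detectable difference is (1.960 + 0.842) × √(1/n₁ + 1/n₂): 0.886 SD at 20:20 and 0.904 SD at 24:16.

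**Predictability.** Suppose an observer knows the block size, the block boundaries and all earlier allocations. Count the positions at which only one assignment remains possible.

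- A, 10 equally likely orders. Position 3 is certain if both minority places have gone (1/10). Position 4 is certain if the first three are all majority (1/10) or both minority places are used (3/10). Position 5 is always certain. Sum: 0.1 + 0.4 + 1.0 = 1.5 per block, or 12 of 40 (30%). Best guessing is right 72% of the time.
- B, 20 equally likely orders. Position 4 is certain only after three alike (2/20). Position 5 is certain only if the first four ran 3:1 (8/20); after 2:2 it is a coin toss. Sum: 0.1 + 0.4 = 0.5 per block, or 4 of 40 (10%). Best guessing is right 62% of the time, against 50% by chance.
- C lies between. A block counts as in B until one kind of block is used up, and as in A afterwards. The final run of like blocks averages 1 + 3/7 + 6/42 + 6/210 = 1.6 blocks, each adding 1.0 certain allocation: 8 × 0.5 + 1.6 = 5.6 of 40.

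Balance and predictability figures must be read within one scenario. The 27% and 29% belong with 4 of 40; the 12 of 40 belongs with 24:16.

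**Alternatives.**

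| Scheme for 40 patients | Balance within blocks | Certain in advance if the structure is fully known |
| --- | --- | --- |
| Ten fixed blocks of 4 | 1:1 | 10 × 1.333 = 13.3 |
| Five fixed blocks of 8 | 1:1 | 5 × 1.6 = 8 |
| Four of 4 and four of 6 | 1:1 | 4 × 1.333 + 4 × 1.5 = 11.3, only if the order of sizes leaks |

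An even size alone restores balance. It does not remove predictability.

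**The case against.** The imbalance has little consequence. An overall 20:20 is possible, section 5.1 does not rule out four blocks of each kind, and the worst split costs about 4% in variance. The protocol promises equivalent groups, not equal numbers. All of this stands, and balance alone would not carry the point.

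Predictability is not peculiar to five. Fixed blocks of 4 would be more predictable, the operator cannot be blinded, and section 5.8 discloses this. That also stands, but disclosing that the perfusionist knows the therapy does not conceal the next allocation. Block size is something that the plan can still change.

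A reader might infer more than the text supports:

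- That the investigator is the perfusionist. Sections 5.6 and 5.8 make this plausible but do not state it.
- That the block size was public or known to those enrolling. The protocol does not say who enrols, who holds the list, or who knows the block structure.
- That the last allocation of every block can be deduced. This holds only if the block's make-up is known. With a random majority it holds in 40% of blocks.

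The consecutive series in section 5.6 also limits selective entry. It does not remove it, because exclusions in section 5.5.2 are settled only during surgery.

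**Conclusion.** The point holds in a limited form and should be fixed. It is certain that a block of five cannot be 1:1 between two arms, and that section 5.1 leaves the ratio and the make-up open. The resulting split is between 20:20 and 24:16, with a loss of about 4% in variance at most.

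The more important part is conditional. If those who enrol know the block size and boundaries, between 4 of 40 allocations (majority random) and 12 of 40 (known 3:2 throughout) are certain beforehand. The documents do not show that this knowledge existed or was used. They do show a fixed size in the protocol, an operator who sees every allocation, and eligibility not fully settled before bypass. They do not support a conclusion that allocation was foreseeable as a matter of fact, or that the arms will be unequal.

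**What to change.** In section 5.1, replace the blocks of five with 1:1 blocks of even, varying size in random order. Four blocks of 4 and four of 6 give 16 + 24 = 40 patients and keep eight blocks. State the 1:1 ratio in the protocol, but keep the block sizes in a separate document not available to those who enrol or run bypass. As the 11.3 of 40 shows, the protection comes from keeping the order of sizes hidden.

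Name someone outside enrolment and perfusion to generate the list and conceal it, for example in sealed envelopes. If this is done on the data analyst's side, use coded arms so that the analyst stays blinded. Section 6 describes the university resource as essentially computer and statistics software, so a list-holding service there cannot be assumed.

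The cost is a new list and a named person to hold it, with no extra patients. The change does not affect exclusions judged during bypass, when the current patient's arm is already known to the perfusionist. Record those by arm with the reason.
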